### Limitations

This study recruited an internet population of health care providers in the United States–Mexico border region; therefore, findings may not directly translate to other health care provider populations nationally or globally. Furthermore, this intervention did not provide Continuing Medical Education (CME) credit, which would limit uptake outside of an RCT setting. Study participation involved a relatively large time commitment for providers in practice, which worked against recruitment and survey completion. We may, therefore, be somewhat limited in our ability to conduct subanalyses such as comparisons across provider specialties (eg, pediatrics vs family medicine) or other participant characteristics (eg, ethnicity or income level). As we have gathered data from health care providers in medicine, nursing, and pharmacy, different approaches to patient care in these professions may increase variability in the responses obtained. A pretest of HPV and vaccine-associated practices was not done in our study, and the use of solely self-reported data may be incomplete or may contain bias. Our random assignment of participants into control and experimental groups should protect against baseline group differences; however, we will still be able to determine the persistence of any changes in behavior regardless of participant starting point. If any group of providers demonstrates high vaccine recommendation rates at the onset of the study, it will be difficult to determine a statistically significant increase in behavior in response to the intervention. Still, identifying providers with strong recommendation practices will be of benefit to our project. Finally, we anticipate the loss of a limited number of participants through attrition over time for many possible reasons, perhaps reducing the power of our study and our data analysis capabilities at the 3- and 6-month time points.

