**Methods:**

We will conduct a randomized, blinded, multiple posttest-only controlled behavioral trial using a parallel group design that will examine the effectiveness of a fully automated, web-based, culturally tailored HPV education and professional skills intervention containing unique reading material and video role-play, as compared to a standard Centers for Disease Control and Prevention fact sheet and video about general communication skills. Participants were recruited using a purposive sampling technique, both internet-based and in-person outreach events. Study data are being collected and managed using REDCap (Research Electronic Data Capture; Vanderbilt University) hosted at the University of Texas at El Paso. Chi-square analyses, ANOVA, and other statistical tests will be used with 2-tail α to reject null hypotheses at .05 to analyze the self-assessed outcome data. The Mauchly test of sphericity for each ANOVA and the Huynh-Feldt epsilon test or Greenhouse-Geisser correction to the degrees of freedom of the F-ratio will be reported for each significant effect. We may use multiple imputation procedures to handle the missing data (if applicable). This study is being conducted in the west Texas or southeast New Mexico region of the United States. Chi-square analyses will be used to assess associations between variables reported on the baseline provider knowledge, attitudes, and practice scales. We seek to examine self-assessed changes in provider attitudes and behaviors regarding HPV vaccine recommendation 1 month after receiving our unique multimedia and culturally tailored intervention.

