#### Demographic and Background Questionnaire

The demographic and background questionnaire via the REDCap platform will gather demographic information (eg, age, gender, ethnicity, and income), as well as information about family composition, HPV vaccination status, trusted sources for medical information, general feelings about vaccines, trust in the government, and experiences with the recent COVID-19 endemic [22]. The demographic survey will only be administered at baseline prior to administering the intervention. The demographics survey requires approximately 5 to 8 minutes to complete.

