#### Postassessment

A post-assessment via the REDCap platform will be administered at baseline (immediately following intervention), 3 months, and 6 months [22]. The post-assessment will include a modified version of the VAKS [13,21] to self-assess factors that influence levels of comfort in discussing HPV-related topics, patient-provider communication about HPV, vaccines, cancer risk, and additional questions designed to evaluate the impact of the interventions and the actual changes in practice in terms of vaccine uptake, patient communication, and vaccine recommendation behavior. Moreover, the outcome variables are included in the post-assessments such as the self-assessment of the proportions of provider practices (as indexed by the HCP practices scale), provider beliefs (as indexed by the HPV vaccine attitudes scale), and provider knowledge (as indexed by the HPV knowledge scale). These will be measured on previously published scales adapted from the VAKS [13,21]. In a previous study that administered the VAKS, Cronbach α ranged from 0.70 to 0.90 for the various scales included in the survey [13]. The post-assessment requires approximately 25-30 minutes to complete.

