### Study Outcomes

The chi-square analyses will be used to assess associations between variables reported on the baseline provider knowledge, attitudes, and practice scales. Repeated measures mixed ANOVA with α set to .05 will examine whether change in our outcome variables (self-assessment of the proportions of provider practices, as indexed by the HCP practices scale), provider beliefs (as indexed by the HPV vaccine attitudes scale), and provider knowledge (as indexed by the HPV knowledge scale) is the result of the interaction between the experimental condition (tailored intervention vs active control) and time (at 3 time points) [23]. If no interaction emerges, we will conduct follow-up tests to determine whether any change in our outcome variables are due to one of the factors (experimental condition or time). We will calculate the Mauchly test of sphericity for each ANOVA, and the Huynh-Feldt epsilon test or Greenhouse-Geisser correction to the degrees of freedom of the *F*-ratio will be reported for each significant effect [23-25]. We may use multiple imputation procedures to handle missing data (if applicable).

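### With no practice score before the module, persistence of behavior change cannot be determined whatever the starting point; only the between-arm difference can be followed over time

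*Protocol article*

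**What the plan says.** The abstract calls the study a "randomized, blinded, multiple posttest-only controlled behavioral trial". The Postassessment section places the practices, beliefs and knowledge scales in a survey "administered at baseline (immediately following intervention), 3 months, and 6 months", so the time point labelled baseline already follows the module. The questionnaire given beforehand covers demographics and background: "The demographic survey will only be administered at baseline prior to administering the intervention". It lists no practices scale.

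The Limitations section confirms this: "A pretest of HPV and vaccine-associated practices was not done in our study". It then says that random assignment should guard against differences between the groups at the start and, in the same sentence, that "we will still be able to determine the persistence of any changes in behavior regardless of participant starting point". The next sentence begins "If any group of providers demonstrates high vaccine recommendation rates at the onset of the study" and warns that an increase would then be hard to show.

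The analysis under Study Outcomes is a repeated measures mixed ANOVA that tests condition by time over the three surveys. If no interaction emerges, follow-up tests ask "whether any change in our outcome variables are due to one of the factors (experimental condition or time").

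**The concern.** Persistence of a change presupposes that a change took place. Showing that for a provider, or for one arm alone, needs a level from before the module, and none is recorded. A provider who scores 4, 4, 4 may have risen to 4 and stayed there, or may always have been at 4.

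The risk lies in interpretation. If neither module does anything, stable scores are what one expects to see. The Limitations wording would let a report present that stability as improvement that lasted. In the other direction, a real effect already present at the first survey could be set aside as a high starting level, because the first practice score comes after the module.

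**Working it through.** The plan attaches no figure to this claim, so there is none to reproduce. The check is one of identifiability, followed by an illustration in the planned model.

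**Identifiability.** Let m be the mean practice score before the module. Randomization makes it the same in both arms in expectation. Let d_T(t) and d_C(t) be the change from that level in the tailored and control arms at t = 0, 3, 6 months. The observed means are

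- tailored: m + d_T(t)
- control: m + d_C(t)

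This gives six observed means and seven unknowns (m and six changes). Adding a constant c to all six changes and subtracting it from m leaves every observed mean as it was. It follows that:

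- Change within an arm, d_T(t) or d_C(t), is not identified. Nor is change common to both arms.
- The difference D(t) = d_T(t) - d_C(t) is identified at each time, because m cancels.
- The time term uses contrasts such as the arm-averaged d(6) - d(0). A change that is fully kept gives zero, and so does no change.
- The interaction uses contrasts such as D(6) - D(0). A between-arm difference that is fully kept also gives zero.
- The condition term averages D(t) over the three surveys, so a kept difference appears there.

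**Illustration.** Inputs from the document: 128 recruited and 1:1 allocation, so 128 / 2 = 64 per arm (no attrition applied); three time points; two-sided alpha .05. Assumed: SD 1, within-person correlation 0.5, means as listed. There were 4,000 runs per scenario.

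| Scenario (level before the module is never observed) | Interaction | Condition | Time |
|---|---|---|---|
| (a) Nobody changed; 3.5 throughout in both arms | 5.7% | 4.8% | 5.8% |
| (b) Both arms rose from 3.0 to 3.5 and kept it | 5.5% | 5.3% | 5.5% |
| (c) Only the tailored arm rose, by 0.5, and kept it | 5.2% | 92.8% | 5.1% |
| (d) Tailored-arm gain of 0.5 lost by month 6 (4.0, 3.75, 3.5 against 3.5) | 72% | 40% | 73% |

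Rows (a) and (b) have identical data distributions, so their small differences are simulation noise. No analysis of these scores can tell them apart, whatever the correlation.

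Row (c) can be checked by hand. The variance of a provider's mean of three scores is (1 + 2 x 0.5) / 3 = 0.667. The standard error of the arm difference is sqrt(0.667 x 2 / 64) = 0.144, and 0.5 / 0.144 = 3.46. Against a critical value of about 1.98, power is about 93%, which agrees with the simulation.

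Row (d) shows what the interaction and time terms do detect: movement after the first post-module survey.

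**The case against.** **The sentence opens with randomization.** It can be read as a claim about persistence between arms, and the hypothesis and primary outcome are also between-group. That reading is sound as far as it goes, and the difference can be followed. The wording goes further: it covers any change and makes each participant's starting point irrelevant, which randomization does not deliver.

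**The planned model is not blind to persistence.** A reader might infer that time is the only trajectory analysis, or that the ANOVA has nothing to say about persistence. The document does not support that. The interaction is tested first and the condition test is a named fallback; rows (c) and (d) show both picking up between-arm patterns.

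**The surveys ask about change directly.** The follow-up surveys include items on how behavior has altered after the module, and the Postassessment section lists questions on actual change in practice. These are a stated source of information. They are retrospective self-reports, are not named in the Study Outcomes analysis, and do not supply a score from before the module.

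**The first score may describe earlier habits.** The practices scale asks about frequency, and the first survey comes straight after a 15-30 minute module, so little practice can fall in between. If those items look back, the 0-month score would serve as a rough baseline. The recall window is not given, and the hypothesis expects a between-arm difference at 0 months, so the document does not settle this.

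**Ceiling remark.** A reader might also see a contradiction between the persistence claim and the warning about high initial rates. They can both hold: one concerns room to detect an increase, the other maintenance over follow-up. What remains is that an onset level is referred to without a measurement known to precede the module.

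**Conclusion.** The claim is too strong as written. With post-module scores only, neither persistence of change within a provider or an arm nor change common to both arms can be determined. This follows from the timing of the surveys and depends on no assumed SD or correlation. The rejection rates above do depend on those assumptions and serve as illustration only.

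Persistence of the tailored-minus-control difference can be determined. If it is constant, it shows in the condition effect and not in the interaction or time terms.

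The point limits what the trial may conclude; it does not invalidate the primary comparison. A reader might infer that the investigators intend to report a null time effect as lasting improvement. Nothing in the analysis or results sections says so, and the Limitations section openly discloses the missing pretest. The conclusion about the 0-month score would soften if the practices items proved to describe behavior before the module.

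**What to change.** - **Limitations:** drop the phrase that makes the starting point irrelevant, and limit the claim to persistence of the difference between tailored and control arms.
- **Study Outcomes:** report the tailored-minus-control difference with its 95% CI at 0, 3 and 6 months, and base any statement on persistence on these. The 0-month contrast belongs here because the hypothesis names it. Treat the time main effect and within-arm profiles as description of drift after the module.
- **High starters:** do not identify them from the 0-month score unless the recall window of the practices items shows that it describes behavior before the module. State that window.

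Cost: the within-arm persistence claim is given up and three contrasts are added. Recruitment is closed, so a pretest cannot be added, but no new data are needed, and analysis was still in progress in March 2025. With 64 per arm and all scores present, the standard error of one contrast is sqrt(2 / 64) = 0.177 SD, so the 95% CI half-width is about 1.98 x 0.177 = 0.35 SD. At 15% attrition (128 x 0.85 = 108.8, about 54.4 per arm) it is about 1.98 x sqrt(2 / 54.4) = 0.38 SD.

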### Conclusions

To improve population health, it is essential to look beyond interventions aimed solely at patient populations. Web-based educational programs for health care professionals are promising tools for enhancing the real-world implementation of CPGs. Tailoring these provider-level interventions to account for regional and patient population characteristics can also improve patient-provider communication as clinical guidelines evolve. Until HPV and other vaccine-preventable infections are eradicated, collaboration between health researchers and providers is critical to delivering accessible and effective professional development interventions. Furthermore, beyond reporting research findings of such studies, reporting specific intervention protocols helps ensure transparency in the research process and facilitates the improvement of population health interventions.

## Data Availability

The datasets generated or analyzed during this study are not publicly available as they are stored in the REDCap (Research Electronic Data Capture) repository maintained by the University of Texas at El Paso and subject to institutional access restrictions but are available from the corresponding author on reasonable request.

## Appendix

Multimedia Appendix 1 CONSORT-eHEALTH checklist (V 1.6.1).

Multimedia Appendix 2 Peer-review report from the External Advisory Committee for the National Institutes of Health (NIH) Research Centers in Minority Institutions (RCMI) Program - Border Biomedical Research Center at the University of Texas at El Paso (National Institutes of Health, USA).

## Abbreviations

CDC: Centers for Disease Control and Prevention
CME: Continuing Medical Education
CONSORT: Consolidated Standards of Reporting Trials
CONSORT-EHEALTH: Consolidated Standards of Reporting Trials of Electronic and Mobile Health Applications and Online Telehealth
CPG: clinical practice guideline
HCP: health care provider
HPV: human papillomavirus
LGBTQ+: lesbian, gay, bisexual, transgender, and queer/questioning
RCT: randomized controlled trial
REDCap: Research Electronic Data Capture
VAKS: Vaccine Attitudes and Knowledge Survey
